## Design and methods

This will be a single-centre, double-masked randomised controlled crossover trial. There will be a 50:50 allocation ratio to evaluate the superiority of a hypothetically optimal intervention over a sub-optimal intervention.

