### Intervention description

The proposed double-masked RCT has five phases (Fig. 1). For a more detailed account of the procedure, please see Additional file 2.Participant recruitment follows three stages (see Additional file 2).Colorimetry, WRRT, and prescribing PTL interventions. Participants will be randomly allocated (with masking) to wear first either optimal (active) colour or sub-optimal (control) colour.Short-term effects of the first pair of PTL:Wilkins Rate of Reading Test (WRRT) at dispensing of first pair (first PTL vs no tint): The test will be administered (following test instruction manual) twice in each condition in the order ABBA with random allocation of PTL or no tint to A or B.Symptoms with the first pair from diaries (see Additional file 5) throughout 1 month of wear and a questionnaire at the end of the month.Academic behaviour survey completed by parents and teachers (see Additional file 6) in the last week of 1 month of wear.After a washout period, each participant will crossover to the other pair, and the researcher will assess the short-term effects of the second pair of PTL, as described in (3) above, including WRRT with second PTL vs no tint in ABBA order.After both pairs have been worn, participants will return for:WRRT with first PTL vs second PTL in ABBA order with random allocation to A or B.The researcher (maintaining masking) will compare symptom diaries from (3) and (4) and WRRT data to decide with the participant about the preferred pair to be dispensed to participants who wish to keep one pair.

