#### Tertiary outcome measures

The tertiary outcome measure will assess reading speed using the WRRT. The WRRT will be measured before prescribing PTLs, with each pair of PTLs, and at the end of the clinical trial in phase 5, as described above. To reduce variability and assess reliability, the test will be administered twice in each condition (with or without tints). The testing order will be ABBA, with A randomly allocated to one of the conditions.

Previous studies have shown that for participants with VS, PTLs and IOs increase reading speed [25, 37] measured on the WRRT. Conventional reading tests [38] are designed for educational use to assess long-term improvement and are commonly used to estimate reading age. These educational tests often use large print that is visually unchallenging and are not suitable for assessing the immediate short-term effect of optometric interventions.

In contrast, the WRRT was designed not for educational use but to assess the immediate effect of optometric interventions [25, 37] and comprises four passages, each taking 1 min to administer. This approach is highly relevant in measuring the effect of PTLs. Research reveals that the WRRT is a valid measurement of within-subject treatment effects and, therefore, well-suited to the research [25].

The specific measurement variable will be scored on a quantitative scale representing the number of words read correctly in 1 min on the WRRT with pair A vs pair B. The analysis will be carried out at the end of the 3-month trial, as participants will complete the WRRT throughout the trial, administered at baseline (referring to the situation before interventions) and at the end of each wearing period (referring to the situation with each intervention). The method of aggregation will be to compare the number of words read and will reveal whether pair A or pair B created the greatest reduction in VS symptoms.

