## Assignment of interventions: allocation

### Sequence generation

The sequence generation will use block randomisation, with blocks of 4, from www.sealedenvelope.com. The use of blocks of 4 means that as long as the number of participants is a multiple of 4, there will be an equal number of participants wearing each intervention in the first period (balanced design).

Participants will be told that 50% of participants will receive the optimal colour first and 50% will receive a slightly different colour first. Each participant will swap to the other colour after 1 month of wear.

When the specification of both tints has been determined at the colorimetry assessment, the participant will choose a spectacle frame in which either the optimal or sub-optimal tint will be glazed. A technician (not the research optometrist) will check the frames, lens optical properties, and tint. Each participant will be provided with one spectacle frame which will be reglazed to the other tint at crossover.

The researcher, participants, parents, teachers, etc., will be masked as to whether each participant receives the optimal or sub-optimal tint first. This is possible because during colorimetry, when each colour is selected, colours are changed slowly so that the person being tested adapts to the colour and therefore is unlikely to be aware of the difference in colour appearance of the optimal and sub-optimal tint. Further, participants will receive the first pair of spectacles some weeks after colorimetry, so they will be likely to have forgotten their detailed perceptions during colorimetry.

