Initially, all data will be checked by scatter plots of raw data. All data will be tested for normality using the Shapiro-Wilk test, and non-parametric data will be transformed to parametric where possible. Simple comparisons will use paired *t*-tests, or the Wilcoxon signed-rank test as appropriate. For more complex analyses, a Mixed-Effects Model for Repeated Measures (MMRM) will be carried out to account for the crossover design, including fixed effects (intervention type, period, and sequence) and random effects (participant variability).

A confirmatory check will be performed to test for order effects (e.g. whether participants who have the optimal tint after the sub-optimal tint have a statistically different outcome from those who have the sub-optimal tint after the optimal tint). If such an effect is found, key analyses will be repeated whilst controlling for the order effect. In addition, an analysis of the effects of the first tint alone will be compared across participants. The analysis will have low power and will be confirmatory, but it is independent of order effects.

Participants for whom there is a complete set of symptom diary data for at least 2 weeks of wear with both interventions will be analysed on an intention-to-treat basis (ITT) [44]. In the unlikely event that any participants are misallocated, then key analyses will also be run according to a per protocol approach. For the symptom questionnaire conducted before enrolment in the trial and for the academic behaviour surveys, data will only be analysed for participants for whom data are available for *both*interventions [44].

Sensitivity analysis will also be carried out to confirm the robustness of the data produced.

The secondary outcome survey measures will be converted to numeric values. Scores will be aggregated and averaged across surveys and then prepared for statistical analysis using the approaches described above. Tertiary outcome measures will be assessed separately as an exploratory analysis. Tertiary outcome measures will undergo reliability testing using the intraclass correlation coefficient, and analysis for order effects using repeated measures ANOVA, before comparing interventions using standard *t*-tests.

All statistical analyses will be conducted using R (version 4.3.1, R Core Team 2023).

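### The reading-speed t-tests leave out the randomised reading order and wear sequence, so any curved warm-up or recency shift would stay in the error; modelling both is a nearly free improvement

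*Protocol article*

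**What the plan says.** The Statistical methods section gives the WRRT its own route: "Tertiary outcome measures will be assessed separately as an exploratory analysis". It runs from the intraclass correlation coefficient to "analysis for order effects using repeated measures ANOVA, before comparing interventions using standard" t-tests. No order term is named for that last step.

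The design randomises two orders that bear on it:

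- **Reading order within a session.** The Tertiary outcome measures section says "The testing order will be ABBA, with A randomly allocated to one of the conditions". Each condition is read twice. The phase 5 head-to-head, under Intervention description, is "WRRT with first PTL vs second PTL in ABBA order with random allocation to A or B".
- **Wear sequence.** Sequence generation says "The sequence generation will use block randomisation, with blocks of 4", with 1:1 allocation.

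Elsewhere the Statistical methods section describes a mixed model with intervention, period and sequence for more complex analyses. It also promises to repeat key analyses with control for order if an order effect is found. Neither provision names the WRRT.

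**The concern.** A factor that the trial randomises, and that may shift the outcome, normally belongs in the analysis. Here two such factors are left out of the final comparison.

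ABBA protects against a steady trend over four readings, but not against a curved one such as a slow first reading. Under a curved trend, the tint read in positions 1 and 4 is shifted against the tint read in positions 2 and 3, with a sign set by the randomised reading order.

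In phase 5 the second tint has just been worn for a month. The first was last worn about two months earlier (one month of washout plus one month of the second period). Any effect of that recency has a sign set by the wear sequence, and ABBA does nothing about it.

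What is at stake is the precision of the trial's only same-session comparison of the two tints, and the width of its confidence interval.

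**Working it through.** **Inputs from the article.** 88 evaluable children before the withdrawal allowance to 120; two-sided 5% level; two readings per condition; wear sequence in blocks of 4; reading order randomised, with no statement that it is balanced. The 88 can be reproduced. The printed formula gives 2(1.2816 + 1.9600)²/0.5² = 84.06, so 85. The noncentral-t version, with standardised difference 0.5/√2 = 0.354, gives 87, or 88 when rounded to an even number or a multiple of 4.

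**Assumed, because the article gives no figure.** The WRRT's SD, the sizes of the two shifts, and a true tint difference of 0.30 residual SD.

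**Step 1: what ABBA removes.** The contrast is the mean of positions 1 and 4 minus the mean of positions 2 and 3.

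- Linear drift (0, 1, 2, 3): 1.5 − 1.5 = 0.
- Slow first reading only (−1, 0, 0, 0): −0.5, so half the deficit stays.
- Fading warm-up (−1, −0.5, −0.25, −0.125): −0.5625 + 0.375 = −0.19.

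In BAAB each sign is reversed.

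**Step 2: the model.** Let y be a child's mean of two readings with the optimal tint minus the mean of two with the sub-optimal tint:

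y = τ + d·o + r·s + e

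Here o = ±1 (optimal tint in positions 1 and 4, or 2 and 3) and s = ±1 (optimal tint worn second or first). The shifts d and r are in units of the SD of e.

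- A paired t-test on y estimates its error variance as about 1 + d² + r².
- With wear sequence balanced by blocking, r cancels from the mean of y. With reading order randomised without balance, d does not fully cancel. The actual variance of the estimate is then proportional to 1 + d².
- With both factors in the model, the error variance is 1.

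**Step 3: power at 88 children, true difference 0.30.** With both factors modelled and both orders balanced, the noncentral t with 85 df gives 79.5%. The t-test figures below are simulated with wear sequence balanced and reading order unrestricted. The exception is the 0.1 row, which is the noncentral-t value at variance factor 1.02.

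| d | r | Variance the t-test reports | Actual variance | Power of t-test |
|---|---|---|---|---|
| 0.1 | 0.1 | 1.02 | 1.01 | 78.7% |
| 0.2 | 0.2 | 1.08 | 1.04 | about 77% |
| 0.3 | 0.3 | 1.18 | 1.09 | 73 to 74% |
| 0.5 | 0 | 1.25 | 1.25 | about 70% |

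**Step 4: validity.** In a simulation of 88 children with the same balance, the t-test's type I error was 3.9% with both shifts at 0.3 SD and 3.0% with both at 0.5 SD. The model gave 4.9% and 4.8%. The conservatism comes from the balanced factor, whose shift is in the reported standard error but not in the estimate.

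**Step 5: cost if both shifts are zero.** With balanced orders, two degrees of freedom cost about 0.02 points of power. If reading order is unbalanced by chance, its expected squared imbalance is 1/88 = 0.011, so the variance of the adjusted estimate rises by about 1.1%. Power then lies between 79.5% (factor 1.00) and 78.7% (factor 1.02), a cost of about half a point.

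**The case against.** The best reply is that nothing here is invalid. A paired t-test on a randomised, counterbalanced comparison is sound, the outcome is exploratory with no power claim, ABBA already removes linear drift, and by phase 5 the children have met the test several times. The article also presents the WRRT as a measure of immediate effect, and nothing in it shows that a month of prior wear shifts the score. All of this stands, and it limits the point to an efficiency gain of unknown size.

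The reply that order is already handled stands only in part. The promise to repeat analyses with control for order applies only once an order effect has been detected, is limited to key analyses and is illustrated by wear order. It does not clearly reach an outcome assessed separately. The mixed model has no reading-order term.

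Stronger readings that a reader might infer, and that the document does not support:

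- **That the comparison is biased.** While the orders stay balanced, both shifts average out. Bias in the realised estimate needs the orders to become unequal, for example through losses.
- **That information worth several children is lost.** Dividing 88 by 1.08 or 1.18 suggests about 81 or 75 effective children. With wear sequence balanced by blocking, the recency part inflates the reported standard error and does not lose information, so these figures do not hold.
- **That warm-up and recency effects exist.** No section reports either.
- **That standard means unpaired.** The article does not say so, and the same section names paired tests for simple comparisons.

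**Conclusion.** The point holds as a minor, nearly free improvement. The plan fixes a final WRRT comparison without two factors that the trial itself randomises, and gives the order-effects ANOVA no consequence for it. The result is a valid test that would be less precise, through any reading-order shift that is not balanced out, and conservative, through any recency shift.

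The loss is under one point of power if both shifts are 0.1 SD, about 2 points at 0.2 SD each, about 6 points at 0.3 SD each, and about 9 points for a reading-order shift of 0.5 SD alone. These figures rest on 88 children, an assumed true difference of 0.30 residual SD, balanced wear sequence and unrestricted reading order. The document cannot say which row applies. At 0.1 SD or less the choice makes almost no difference either way.

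**What to change.** In the Statistical methods section, replace the final WRRT t-test with a linear model of each child's within-session difference (mean of two readings per condition). Include reading order and wear sequence as fixed factors, each centred as ±1, whatever the ANOVA shows. Take the tint effect and its confidence interval from that model's intercept.

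Code reading order by which tint, under the masked labels, held positions 1 and 4. In phase 5 the letters in ABBA refer to the first and second pair. Coding by pair would not line up with the sign of the warm-up shift in the tint difference.

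The cost is a change of wording and two degrees of freedom, plus about half a point of power if reading order is unbalanced by chance and neither shift exists. Both orders are already randomised, and the Trial status section says that recruitment has not begun.

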### Interim analyses

There will not be access to interim results.

### Plans to give access to the full protocol, participant-level data, and statistical code

After data analysis, the de-identified results will be placed in a public repository for access by other interested researchers.

### Composition of the coordinating centre and trial steering committee

The first five co-authors of this manuscript will fulfil the roles of a trial steering committee. The lead researcher (ZR) will provide organisational support, meeting with other members of the research team monthly to ensure that the study is well-conducted.

### Composition of the data monitoring committee, its role and reporting structure

The intervention under investigation (tinted lenses) is safe, and the sub-optimal colour, although not the optimal colour, will be chosen as a similar colour that is unlikely to cause significant symptoms compared with no tints. However, as a precaution, all participants will be told, in writing (in the PIS) and verbally, that they can discontinue wear at any time. Given this precaution and the safe nature of the intervention, it is thought that a data monitoring committee is not needed. The interventions are safe (PTLs), and participants will be informed (verbally and in writing) that they can stop wearing the coloured lenses at any time.

### Adverse event reporting and harms

The risks of harm are very low, and there is no ophthalmic drug intervention. Full optometric testing, which is a key part of this clinical trial, involves tests widely used in routine optometric practice. PTLs are designed to reduce symptoms of visual stress and improve reading speed. However, in the unlikely event that there is a marked increase in symptoms or reduced reading performance, affecting behaviour or academic outcomes, the participants can stop wearing the PTL and drop out of the trial. There have been no studies showing this effect.

### Frequency and plans for auditing trial conduct

This work is a doctorate project for ZR. The on-campus supervisory team, led by PA, will audit the research records for approximately every fifth participant.

### Plans for communicating important protocol amendments to relevant parties (e.g. trial participants, ethical committees)

Protocol amendments will be discussed within the research team, and if it is agreed they are essential, approval will be requested from the ethics committee. The trial registry will be updated.

### Dissemination plans

The study protocol has been presented at an international conference (European Academy of Optometry and Optics, 2022) and is being published herewith. The results will be presented at one or more international conference(s) and published in one or more peer-reviewed journal article(s). Any participants who express an interest in the results will be invited to email ZR who will send a de-identified summary of the main findings in lay language.

## Discussion

A protocol is outlined for a double-masked, randomised, controlled, crossover clinical trial (RCT) involving young people aged 9–18 years who meet contemporary diagnostic criteria for VS. The trial will investigate whether PTLs prescribed using the IS are beneficial. Systematic reviews [13, 20] in 2016 criticised the lack of consistent diagnostic criteria and in response criteria were published in 2017 [2]. This clinical trial will be the first study of children to adopt these diagnostic criteria. Both major reviews on this topic agree that more clinical trials are required to establish whether PTLs confer a clinical benefit in the treatment of VS.

A strength of this study is the decision to use symptoms as the primary outcome measure, which is strongly justified by the literature, and the development of a symptom questionnaire based on the literature to identify and quantify symptoms of VS. VS is a construct that is not observable or measurable directly; in statistical terms, it is a latent variable that is accessible only through certain measurable indicator variables, such as the frequency/severity of symptoms. Therefore, to support the idea that the overarching construct is valid, there was a requirement for a symptom questionnaire to be created with several VS indicators from published research [2, 10, 13]. A symptom questionnaire for VS has recently been developed for adults [45], but none is available for children and hence the development of the approach described in Methods.

A notable strength of this study is its pragmatic design, which allows data collection to occur across different phases of the school academic year, depending on the date of participant enrolment, as the study extends over 3 months. This introduces natural variation in academic and visual demands, creating differences in PTL usage and reflecting real-world use of PTLs. It captures the potential benefits of PTLs in managing VS symptoms during study-related tasks and daily visual activities. This design enhances the generalisability and real-life relevance of the results. For practical reasons, all participants will not start at the same time, but rather, enrolment in the study will be staggered over many months. Therefore, randomisation of tint allocation to wear period will average out any effects of holidays.

Another strength of this study is the potential impact on society. If an individual suffers from symptoms of visual distortion, headaches, and eyestrain when reading, there is likely to be a tendency to avoid reading which may impact their educational achievement. This RCT will address the core symptoms of VS and help identify whether PTL have an effect on symptoms and WRRT performance in sufferers of VS using the Intuitive System. Improving the understanding of symptoms and potential treatment in those who report the symptoms of VS can provide health care professionals such as optometrists (who will be the most likely to encounter such symptoms in routine eye examinations) to provide patients with advice and, if appropriate, treatment.

Limitations of the trial are as follows. First, there is a risk with a single-site trial within a specialist clinic that the results may not be directly applicable to a more general population. However, the trial will recruit school-age participants from a variety of schools. Additionally, VS is typically treated in specialist optometric clinics, so the choice to base the trial in such a clinic is pragmatic as it reflects typical clinical practice.

Second, due to the requirement for daily diaries and multiple visits, there is a risk of participant attrition. However, the lead researcher aims to develop a positive rapport with participants and send frequent reminders as explained above. The importance of daily diaries lies within the findings of the original 1994 trial [9], where the daily diary analysis produced findings in the original RCT that were statistically significant, justifying a similar approach in this study. The use of reminders by modern technologies (e.g. SMS, WhatsApp, emails) should improve compliance with diary completion compared with the original study.

The results of this RCT aim to strengthen the evidence base concerning the existence and, if appropriate, treatment of VS using the IS.

## Trial status

Ethical approval has been granted by Anglia Ruskin University's ethics. The protocol has been registered at ClinicalTrials.gov https://clinicaltrials.gov/study/NCT06093516?cond=visual%20stress&rank=1.

Protocol version: 20th December 2024 V2.5.

Recruitment has not begun.

Estimated start date: 1st February 2026.

Estimated end date: 1st July 2026.

